## Abstract

**Background:**

With the availability of more advanced and effective treatments, life expectancy has improved among patients with metastatic breast cancer (MBC), but this makes communication with their medical oncologist more complex. Some patients struggle to learn about their therapeutic options and to understand and articulate their preferences. Mobile health (mHealth) apps can enhance patient-provider communication, playing a crucial role in the diagnosis, treatment, quality of life, and outcomes for patients living with MBC. Our team developed an app called My MBC Journey to focus on the collection of important information for patients with MBC between clinical encounters.

**Objective:**

This study will evaluate the usability and satisfaction of My MBC Journey, a mobile app designed for MBC, to inform future modifications.

**Methods:**

This mixed methods study will assess patient use and satisfaction with the My MBC Journey app to inform future app modifications and identify the barriers and facilitators to the app’s use for enhancing patient-provider communication. We will recruit a prospective, cross-sectional convenience sample of 25 patients with MBC and a sample of 15 members of the care team (ie, caregivers, nurse navigators, and medical oncologists). Applying iterative, convergent mixed methods, we will conduct qualitative, semistructured interviews with the patients and care team members. We also will collect quantitative data on usability through app analytics and standardized questionnaires (ie, the Mobile Application Rating Scale, the Mobile Application Rating Scale user version, and the System Usability Scale). Qualitative interviews will be audio recorded and analyzed using NVivo software to identify mHealth implementation themes.

**Results:**

The study’s results will inform future app design modifications and gauge preliminary effect size in support of future evaluations of the app’s efficacy in improving patient-provider communication.

**Conclusions:**

Our long-term goal is to improve patient-provider communication by developing mHealth apps that empower patients to collect and share clinically relevant, patient-reported information in a timely manner.

**International Registered Report Identifier (IRRID):**

PRR1-10.2196/66050

## Introduction

Metastatic breast cancer (MBC) is late-stage breast cancer, where the disease has spread beyond the nearby lymph nodes to other sites such as the liver, lungs, bones, and brain [1,2]. Although men develop breast cancer, MBC most often affects women [3]. It is estimated that 168,000 women in the United States are living with MBC, and that number will likely grow to around 246,000 by 2030 [4,5]. Previously, treatment of MBC was nihilistic in nature, with a major goal of care being palliative. However, with the availability of more advanced and effective treatments, life expectancy has improved among patients with MBC, with over one third of patients now living 5 years beyond their diagnosis and some exceeding 15 years of survival [6,7].

Given the many therapeutic options now available, prolonging survival is a feasible goal for many individuals with MBC; however, it also makes communication with their medical oncologist more complex and essential to the treatment process [7]. Many patients struggle to identify and articulate their preferences for therapeutic options that may help them achieve their personal goals for living with cancer. Current guidelines from the National Comprehensive Care Network involve over 45 treatment regimens for MBC that include chemotherapy (single-agent or combination), hormonal therapy, and immunotherapy [8]. For patients receiving treatment beyond the recommended first-line therapies, the therapeutic combinations present many different toxicity considerations [9]. Beyond the number of potential therapeutic options, communication and decision-making between patients and their medical oncologists is increasingly complex due to competing medical comorbidities and acceptability of treatment toxicities. Patients want to participate in treatment conversations with their medical oncologists, but they often feel overwhelmed by the magnitude of treatment information and how it aligns with their personal goals [6,7]. Additionally, they may undervalue their own insights and are hesitant to ask questions about problematic side effects [6,7]. Patients also must balance the demands of their therapeutic program and its consequences with their health-related social needs, such as housing, food, transportation difficulties, and personal well-being [6,7,10].

Mobile health (mHealth) apps represent a potential tool to facilitate communication between the patient and the medical oncologist. These apps allow the patient to identify, record, and recall information about their well-being, personal goals, and toxicity preferences between clinical visits on their smartphone [11]. Given the high percentage of individuals with a mobile phone that they carry everywhere, the app could assist with recalling and sharing this information during the clinical encounter. Mobile apps also may reach a broader, more diverse patient population, including those who have historically experienced disparities in patient-centered care [11,12]. However, evidence on digital health interventions (DHIs) to improve patient provider communication is limited. A recent systematic review identified only 13 DHIs that targeted improvement of patient-provider communication in cancer care, with just 4 focused on breast cancer. None of these interventions involve delivery through a mHealth app [13]. Additionally, in 2023 we conducted a preliminary review of existing mHealth apps for breast cancer and identified only 1 for MBC that was available in the United States. Upon initial review, this app did not include functionality for a DHI focused on enhancing communication with the provider. In a subsequent review of this app in the fall of 2024, it was no longer available within the app store. With no apps available for patients with MBC in the United States, there is a clear need for continued, evidence-based development of mHealth apps for patients with MBC.  

Our mHealth app, My MBC Journey, was designed to focus on the collection of important information to the patient with MBC between clinical encounters. Collection and organization of information important to the patient may help enhance self-efficacy and build confidence towards communication with the medical oncologist. To design an mHealth app for MBC, our team integrated evidence from qualitative interviews with a human change behavior theory to determine functionality that promotes a patient’s understanding and communication about their health status. The development of My MBC Journey was based on social cognitive theory constructs of self-efficacy and self-regulation [14]. Besides providing the rationale behind the content and functions development process, it is possible to see social cognitive constructs associated with the design of specific resources, such as motivational and personalized messaging and alerts to help people manage their conditions [15,16]. Our app includes the following functionalities: 1) tracking physical, social, emotional, and functional well-being through patient reported outcomes (using the Functional Assessment of Cancer Therapy-Breast and European Organization for the Research and Treatment of Cancer Quality of Life Questionnaire-Breast Cancer 23 instruments); 2) recording personal goals for activities of daily living and treatment preferences for symptom and side effect management; and 3) documenting details about problematic symptoms or side effects in a written, free-form manner. The app also can graphically display patient-reported outcomes (PROs) over the multiple dates where the patient has entered information, thereby demonstrating trends in improvement or decline. It also displays written free-form notes recorded over the same dates as the PROs on top of the graphical display of trends. This novel integration of trends in PROs displayed with the users’ own comments on their health status may help the patient pinpoint how they are feeling at a specific time, thereby enabling more detailed recall and discussion of this information during the clinical encounter. Additionally, having the ability to log goals for activities of daily living and treatment preferences supports the patient in having this information readily available and may enhance their ability to discuss it during the clinical encounter. The app development process, including description of frameworks, screenshots, and functions, is described in depth in a forthcoming paper.

Effective use of mHealth apps as DHIs to improve patient-provider communication hinges on the end users’ engagement with the app and willingness to enter information at a frequency that is clinically valuable. Therefore, as an initial step to app development, this study will evaluate usability and satisfaction with the mHealth app and its barriers and facilitators toward enhancing patient-provider communication. Our specific aims are to assess patient use and satisfaction with the My MBC Journey app to inform future app modifications and to identify the barriers and facilitators to the app’s use for enhancing patient-provider communication.

## Methods

### Study Design

This study will use a prospective, convergent mixed methods design to assess the usability and satisfaction of an mHealth app for patients with MBC that was developed to promote patient-provider communication [17]. We will collect and integrate quantitative and qualitative outcomes on app use and satisfaction with functionality (aim 1). For Aim 2 we will use qualitative, personal interviews to identify barriers and facilitators of the app’s use to determine how it may best be integrated into the clinical care setting to enhance patient-provider communication [18]. We will seek both the patients’ and the care team members’ perceptions. The results will inform modifications to our mobile app that will then be ready for future, iterative usability testing and eventual evaluation of the app’s efficacy to enhance patient-provider communication (Figure 1).

**Figure 1 figure1:**
[figure not shown]
Study design. MBC: metastatic breast cancer; mHealth: mobile health.

### Participants and Recruitment

Patients with MBC and their care team members are eligible to participate in this study. Aim 1 will require a prospective, cross-sectional convenience sample of 25 participants with MBC. Aim 1’s recruitment inclusion criteria are as follows: patients aged 19 years or older who are able to speak and read English, have clinically-documented MBC, possess a mobile device on which the mHealth app for MBC can be installed (Android or iOS operational systems), have a visit with their medical oncologist within the next 4 months, and are able to provide written informed consent. Exclusion criteria are participants who decide with their oncologist to enter hospice care. Similar criteria have been used in previous studies determining mobile apps’ usability by patients with other diseases [19].

Aim 2 requires a prospective, cross-sectional convenience sample of care team members who provide oncologic care to the study participants recruited in aim 1. A sample of 15 care team members will be recruited. A breast cancer care team may consist of medical oncologists, nurse navigators, informal caregivers, radiation oncologists, psychiatrists, physiologists, nutritionists, social workers, and integrative therapists, among others [20]. In this study, eligible care members include medical oncologists, nurse navigators, and informal, patient caregivers because they are most likely to assist and engage with the patient during usage of the app, and hence, will experience how the apps’ functionality potentially enhances or inhibits patient-provider communication at the point of care.

Our team will partner with the Buffet Cancer Center in Omaha, Nebraska, to register eligible participants over a 7-month period and follow them for at least 1 visit with their medical oncologist. Frequency of visits for patients with MBC is heterogenous, based upon disease severity such as whether it is in an acute or stable phase. Most patients within our setting see their medical oncologist every 3 to 6 months [19]. While this time window may cause different exposure length to the app, it is necessary to support collection of data regarding patients’ perceptions about how the app functions to enhance patient-provider communication in aim 2. Potential patient participants will be informed of the study by their medical oncologist during a regular visit. The medical oncologist and research team will work to ensure diversity across clinical and demographic strata and mitigate sample bias to the extent possible. If the patient is willing to consider participation in the study, the oncologist will give the patient a flyer with written information that explains the study and provides contact information for further details. The contact, referred to hereafter as the study coordinator, will field inquiries (by phone call or text). For the participant who indicates a willingness to participate, the study coordinator will review the aspects of the study and obtain informed consent from the participant during the phone call or a web-based meeting. Once the participant provides informed consent by reviewing and electronically signing the consent form on Research Electronic Data Capture (REDCap) [21], the study coordinator will schedule a meeting to assist the participant in downloading and using the mobile app. 

Care team members also will be recruited from within the Buffet Cancer Center. Medical oncologists and nurse navigators will be informed about the study through flyers posted within the cancer center and snowball recruitment. Informal caregivers will be recruited via nomination of a patient participant in the study, snowball recruitment, or through posted flyers of the study. Care team members may be part of a care team dyad but do not have to be part of that dyad to participate. For care team members who indicate a willingness to participate, the study coordinator will review the aspects of the study and obtain informed consent from the participant during the phone call or a web-based meeting. Once the care team member participant provides informed consent by reviewing and electronically signing the consent form on REDCap, the study coordinator will schedule a meeting to familiarize the care team member with the app and conduct a qualitative interview. Familiarization with the app will occur through demonstrating the major features of the app in a web-based testing environment. Additionally, care team members will be given time to navigate through the app at their own pace and ask questions about how the app works for the patient. During the same session, a study team member will conduct a qualitative interview.

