During the initial use of the app, the participant will provide the independent variables (questions about age, sex, race and ethnicity, education, marital status, income, health-related social needs, and whether they have ever used another health app); the study coordinator will be available to assist the participant as required. As participants use the app, we will obtain outcome measures for aim 1a. After the app use period is completed and the patients with MBC have a visit with the medical oncologist (approximately 4 months), our team will contact the participants (patient and care team member) to schedule the interviews and collect outcomes for aims 1b, 1c, 2a, 2b, and 2c, including, for example, completion of the standardized MARS, uMARS, and SUS questionnaires [22-25]. Interviews will be scheduled for 1 to 2 weeks following the patient’s appointment with the oncologist depending on their availability. The care team members outcomes and independent variables (age, sex, and race and ethnicity) will also be collected during the interviews. Each interview will take up to 60 minutes, and with participant consent, will be audio recorded. The interviews will be conducted by a researcher with a clinical background and extensive experience in qualitative data collection and digital health evaluation. To avoid personal bias, the team member responsible for qualitative data collection will have no previous knowledge, contact, or work experience with the patients or care team members in any capacity.

The audio records will be transcribed using the support of NVivo software (Lumivero) for further analysis. Participants will receive a $30 gift card for participation. 

**Table 1 table1:** Outcome measures.

Outcome		Source of data	Measures	When the outcome is collected
**Aim 1: access patient use of the mHealth^a^ app to inform future modifications using iterative, convergent mixed methods.**				
	1a. Identify the app functions used most often and to what extent	Quantitative data on mHealth app analytics	Events (number of times a page within the app was visited, amount of time participants remained there, and average views on a page per user) and duration (amount of time a patient-reported measure took to complete; assessed using the FACT-B^b^ or EORTC QLQ-BR23^c^)	As participants use the app after initial download.

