	1b. Assess patient perceptions of the app’s aesthetics and content and their sustained engagement with the app	Qualitative personal interviews and quantitative survey questionnaires	Open-ended question prompts (10 items) and uMARS^d^ (20 items)	Within 3 to 6 months after app download during a semistructured personal interview after a visit to a medical oncologist.
	1c. Assess patients’ satisfaction with the mobile app functionality	Qualitative personal interviews and quantitative survey questionnaires	Open-ended question prompts (10 items) and SUS^e^ (10 items)	Within 3 to 6 months after app download during a semistructured personal interview after a visit to a medical oncologist.

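### The eligibility limit, the post-visit interview rule and the Table 1 window are not aligned, because no visit is named as the anchor for the patient interview

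*Protocol article*

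**What the plan says.** The timing of the patient assessment is set in several places in the Protocol article.

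- **Eligibility (Participants and Recruitment, aim 1 criteria).** Patients must "have a visit with their medical oncologist within the next 4 months". There is an upper limit and no lower one.
- **Recruitment and follow-up (same section).** "Potential patient participants will be informed of the study by their medical oncologist during a regular visit". The team will then "follow them for at least 1 visit with their medical oncologist". On usual practice: "Most patients within our setting see their medical oncologist every 3 to 6 months". The section links visit frequency to disease phase, accepts that exposure to the app will vary in length, and aims for diversity across clinical and demographic strata.
- **Interview timing (Study Procedure).** "Interviews will be scheduled for 1 to 2 weeks following the patient’s appointment with the oncologist depending on their availability". The same paragraph describes the typical sequence: "After the app use period is completed and the patients with MBC have a visit with the medical oncologist (approximately 4 months").
- **Table 1, outcomes 1b and 1c.** "Within 3 to 6 months after app download during a semistructured personal interview after a visit to a medical oncologist". Outcome 2a carries the same wording.

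No section says which visit starts the 1 to 2 week clock when a patient has more than one, or what happens when the first visit comes early.

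**The concern.** Two clocks govern one interview. One runs from the oncologist visit (1 to 2 weeks) and the other from app download (3 to 6 months). They agree only if the visit falls in a particular range after download, and the eligibility criterion does not confine it to that range. A patient with a visit one or two months ahead is eligible, yet an interview tied to that visit would fall before Table 1 allows it.

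At the other end, patients are approached at a regular visit and most are seen every 3 to 6 months, but the next visit must be within 4 months. Read at the recruiting visit, that limit shuts out patients with intervals of 4 to 6 months.

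What is at stake is the length of app use behind the main measures. Outcome 1a counts page visits and time, and outcome 1b covers sustained engagement; both depend on how long the patient has had the app. With 25 patients planned and 20% dropout allowed for, a few interviews held at quite different exposures would make the descriptive means harder to read. Site staff would also have to choose which rule to break.

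**Working it through.** **Inputs.** Visit time V, in months after download: eligibility allows 0 to 4. Delay from visit to interview: 1 to 2 weeks (Study Procedure). Required interview time: 3 to 6 months after download (Table 1). Conversion: 30.44 days per month, so 1 week = 0.23 and 2 weeks = 0.46 months. Assumption: download happens close to the eligibility check; step 5 relaxes this.

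**Formula.** Interview time = V + 0.23 to V + 0.46.

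**1. The plan's own typical case.** With V at about 4 months, as Study Procedure describes, the interview falls at 4.23 to 4.46 months. That is inside 3 to 6, so the rules agree.

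**2. The whole eligible range, anchored to the first visit.** V from 0 to 4 gives interviews from about 0.2 to about 4.5 months, against a stated 3 to 6.

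| Visit (months after download) | Interview (months) | Within 3 to 6? |
|---|---|---|
| 1 | 1.23 to 1.46 | no |
| 2 | 2.23 to 2.46 | no |
| 2.5 | 2.73 to 2.96 | no |
| 3 | 3.23 to 3.46 | yes |
| 4 | 4.23 to 4.46 | yes |

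**3. Where the conflict begins.**
- For an interview at the full 2 weeks to reach 3 months: V ≥ 3 − 0.46 = 2.54 months (about 11 weeks).
- For the whole 1 to 2 week span to fit: V ≥ 3 − 0.23 = 2.77 months (about 12 weeks).
- Upper end: V ≤ 6 − 0.46 = 5.54 months for the whole span, or 6 − 0.23 = 5.77 for an interview at 1 week.

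**4. If a later visit may be the anchor.** With interval I between visits, some visit V + k × I must fall between 2.54 and 5.77 months. For the intervals tested of 3 months or less (0.75, 1, 2 and 3), one always does. For longer intervals gaps remain:

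| Interval (months) | First visits with no fitting visit (months) |
|---|---|
| 4 | 5.77 − 4 = 1.77 up to 2.54 |
| 5 | 5.77 − 5 = 0.77 up to 2.54 |
| 6 | any before 2.54 |

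**5. Lag between recruitment and download.** Between the recruiting visit and download come a flyer, the patient's enquiry, consent and a separately scheduled download meeting. The article gives no length for this lag, so it is an assumption. With a 3-month visit interval:
- no lag: visit at 3.00, interview at 3.23 to 3.46 (fits);
- 2 weeks: visit at 2.54, interview at 2.77 to 3.00 (just reaches the limit);
- 4 weeks: visit at 2.08, interview at 2.31 to 2.54 (misses).

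**6. The 4-month limit.** A patient assessed for eligibility at the recruiting visit with a 5-month interval fails it. The same patient assessed one month later has a visit 5 − 1 = 4 months ahead and passes. The article does not say from which date the 4 months run.

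**The case against.** The strongest reply is that the plan works for the patient it has in mind. Recruitment at a regular visit, intervals of 3 to 6 months and a limit of 4 months together point to a next visit at roughly 3 to 4 months, where every rule is met. Study Procedure also makes completion of the app use period a condition for contact, not only the visit. Follow-up may cover more than one visit, so a patient seen early because of frequent visits can be interviewed after a later one. Unequal exposure is openly acknowledged, the analysis is descriptive, and effectiveness is not tested.

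Much of this stands. It defeats several stronger readings that a reader might infer:

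- *The three rules can never be met together.* They can, for visits at about 2.5 to 4 months.
- *Some patients are bound to be interviewed after very short use.* Eligibility leaves room for this, but Table 1 sets a 3-month minimum and nothing forces the first visit to be the anchor.
- *The later part of the Table 1 window can never be used.* A later anchoring visit could use it, and spare room in a window contradicts nothing.
- *Patients with long visit intervals are always screened out.* Those who enquire some weeks after the flyer may qualify.
- *Use and satisfaction are confounded with severity.* No exposure-outcome association is planned, so the effect is on interpretation of the summaries.

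The reply does not close the gap. Using a later visit is a permissible reading, but the article never states it, and step 4 shows that it fails for an early first visit followed by a 4 to 6 month interval. The approximate 4 months in Study Procedure does not bind the eligibility criterion. The acknowledgement of unequal exposure follows directly on the 3 to 6 month visit interval and does not naturally extend to a few weeks of use. Nor is this a detail that an article leaves out by condensing: it states all three rules, and they do not line up.

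**Conclusion.** The concern holds as a misalignment of stated rules. An eligible patient whose anchoring visit falls before about 2.5 months after download breaches either the 1 to 2 week rule or the 3-month lower limit, and the article gives no rule for choosing another visit. The 4-month limit also sits badly with the article's own visit intervals and its aim of clinical diversity if it is applied near the recruiting visit.

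How many patients this touches cannot be derived. A reader might wish to put a share on it, but any figure would rest on an assumed spread of visit intervals: nearly all patients would pass the 4-month limit if intervals clustered at 3 months, and none would if they clustered at 6. The result rests on download close to the eligibility check; a longer lag moves more visits below the threshold. The point should be settled before enrolment because it governs how comparable exposure is across 25 patients. It threatens no inferential result.

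**What to change.** Define one anchoring visit: the first medical-oncologist visit at least about 12 weeks after app download. Earlier visits do not trigger the interview. Keep the interview 1 to 2 weeks after the anchoring visit. The earliest interview is then at 12 + 1 = 13 weeks (91 days), which matches the 3-month start of Table 1. An 11-week minimum would fit only if every interview were held at the full 2 weeks.

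Reconcile the eligibility limit with the Table 1 window and state the date it runs from. An anchoring visit up to about 5.5 months after download still gives an interview by 6 months (5.54 + 0.46). Wording eligibility around the expected anchoring visit also shows at screening which patients would have no visit in the usable range. Use the same definition in Participants and Recruitment, Study Procedure and the patient rows of Table 1 (1b, 1c and 2a), and check the care team rows against it.

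The cost is protocol wording and longer follow-up for some patients: up to about 6 months instead of about 4.5 under first-visit anchoring, so about 1.5 months more, and a wait for a later visit where the first comes early. Clinical visit schedules do not change. The longer follow-up must be carried into the dates in Results. Recruitment there runs to July 2027 and primary analysis is due in August 2027, whereas a patient who downloads the app in July 2027 reaches even the 3-month limit only in October 2027.
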